##### Amount of blood loss

The difference in blood loss in ml within 2 days after platelet transfusion between the study groups will be analysed similarly to the primary endpoint (number of blood products administrated).

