### Study population

#### Inclusion criteria

Participants fulfilling all of the following inclusion criteria are eligible for the study:Age ≥ 18 yearsAdmission to the intensive care unit (ICU)Patients needing platelet transfusion with or without severe bleeding or prior treatment with single or dual antiplatelet agents (ASS, prasugrel, clopidogrel, ticagrelor)Consent by the patient or a family member (non-emergency cases) in addition to the statement of an independent ICU physician

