### Determination of sample size

A total of 120 (each group 60) patients are needed to detect a 50% reduction of the number of blood products subsequently transfused within two days in patients with Wilate® compared to placebo. The sample size is calculated for a power of 80 % and a significance level of 5% for an estimate of the treatment effect evaluated with a negative binomial regression. To improve the precision of the treatment effect, the following covariates will be included: blood loss, number of blood products transfused within 12 h before administration of the study drug, anticoagulants administered 7 days before, the site of bleeding and the level of thrombocytes at baseline. The sample size calculation is based on a simulation applying resampling techniques on historical clinical data of 150 USB patients that meet the inclusion criteria.

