#### Primary analysis

Evaluation of the effect of Wilate® compared to placebo on the outcome number of blood products (TC, EC, FFP) administered using negative binomial regression. The following covariates will be included: blood loss, number of blood products transfused within 12 h before administration of the study drug, anticoagulants 7 days before, the site of bleeding and the level of thrombocytes at baseline.

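### Blood loss in ml is sent by reference to the count model of the primary endpoint, whose model-based standard errors need not hold for a continuous, skewed volume

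*Protocol article*

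**What the plan says.** Under Secondary analyses, the section Amount of blood loss defines the outcome and its method in one sentence. The outcome is "The difference in blood loss in ml within 2 days after platelet transfusion", and this difference "between the study groups will be analysed similarly to the primary endpoint (number of blood products administrated").

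The section Primary analysis gives one method for that endpoint, the "outcome number of blood products (TC, EC, FFP) administered using negative binomial regression", with a list of covariates. Determination of sample size names the same model. No transformation, robust variance or handling of zeros is stated for blood loss.

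Under Definitions/conditions, Quantity of blood loss describes the measurement as a sum of what is collected from chest tubes, reservoirs, drains, suction and rags. The other secondary analyses that have their own section name their own method: a t-test for platelet reactivity, and Cox regression for mortality and hospital stay.

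**The concern.** The negative binomial assumes variance = μ + kμ² and estimates k from the full count likelihood. At hundreds of ml the term μ is negligible and the model behaves like a gamma model with a log link. Its standard error is then right only if the data look gamma.

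Two departures matter, and they act in opposite directions. A heavier right tail than gamma makes the fitted k too small, so the standard error is too small. Exact zeros beside values in the hundreds make the fitted k too large, so the standard error is too large.

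Blood loss is a listed secondary outcome and the most direct measure of the haemostatic effect that the trial claims. The ratio of means would be estimated sensibly, but its interval and p-value could mislead in either direction, and the protocol offers nothing to show which.

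**Working it through.** **Inputs.** From the protocol: "A total of 120 (each group 60) patients", significance level 5% (two-sided assumed), outcome in ml, negative binomial by reference. Not in the protocol and therefore assumed: the shape of the distribution, its mean and the share of zeros.

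**The plan's own figure.** There is no sample size, SD or power for blood loss. The 120 belongs to the primary count: n per arm = (1.96 + 0.84)² × (1/μ0 + 1/μ1 + 2k) / ln(0.5)². For n = 60 the bracket must equal 3.67, for example k = 1.46 at μ0 = 4 and μ1 = 2. That is plausible but cannot be checked, because μ0 and k are not given. It has no bearing on the point here.

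**Formula.** With n = 60 per arm, equal means and negligible 1/μ:
- model SE of the log ratio = √(2k̂/60)
- true SD ≈ √(2·CV²/60)
- for a log-normal with a proportion p of exact zeros, CV² = exp(σ²)/(1−p) − 1

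**One case without zeros.** σ = 1.0 and p = 0 give CV² = 1.718, so the true SD ≈ √(2 × 1.718/60) = 0.239 (0.226 in simulation). The fitted k̂ is 0.85, so the model SE = √(2 × 0.85/60) = 0.168. The simulated ratio of SE to SD is 0.75. Then P(|Z| > 1.96 × 0.75) = P(|Z| > 1.47) = 14.2%, which is also the simulated rate.

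**One case with zeros.** σ = 1.0 and p = 0.20 give CV² = 2.718/0.8 − 1 = 2.40, but k̂ = 3.21. The simulated ratio is 1.19, and P(|Z| > 2.33) = 2.0% (2.1% simulated).

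**Simulation.** 60 per arm, mean 1000 ml among non-zero values, no covariates, 3000 null trials per row:

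| Volumes | Zeros | median k̂ | SE / true SD | Type I, negative binomial | Type I, log-link robust |
|---|---|---|---|---|---|
| log-normal 0.7 | 0% | 0.44 | 0.84 | 10.0% | 6.4% |
| log-normal 1.0 | 0% | 0.85 | 0.75 | 14.2% | 6.3% |
| log-normal 1.3 | 0% | 1.34 | 0.61 | 22.4% | 7.5% |
| gamma, CV 1 | 0% | 0.98 | 0.98 | 5.5% | 6.2% |
| log-normal 1.0 | 10% | 1.90 | 0.99 | 5.7% | 6.7% |
| log-normal 1.0 | 20% | 3.21 | 1.19 | 2.1% | 7.7% |
| log-normal 1.3 | 20% | 3.64 | 0.86 | 8.8% | 8.8% |
| gamma, CV 1 | 20% | 3.32 | 1.49 | 0.4% | 5.3% |

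**With a covariate.** A separate run (600 trials per cell, no zeros) gave about 8%, 12% and 16% unadjusted at log-SD 0.6, 0.8 and 1.0. Adjusting for one prognostic covariate gave 6%, 9% and 14%. The Monte Carlo standard error at 6% is √(0.06 × 0.94/600) = 1.0 point, so that lowest value is compatible with 5%. A further run (1500 trials per cell, covariate explaining 30% of the log variance) gave 9.8%, 11.7% and 15.1% at log-SD 0.8, 1.0 and 1.2.

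**Power with zeros.** At log-SD 0.8, 20% zeros and a 40% reduction, power is 34% to 39% for the negative binomial against 68% to 80% for the robust log-link model, over the unadjusted and adjusted runs. Type I error of the negative binomial is below 1% there.

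**The case against.** **The share of zeros is not established.** Eligibility covers "Patients needing platelet transfusion with or without severe bleeding", and a reader might infer from this that many patients will have 0 ml and that the planned test is therefore badly underpowered. The documents do not support that. The Inclusion criteria under Definitions/conditions tie severe bleeding to a need for at least two red-cell units, so a patient without it may still bleed. Screening and the hypothesis in the Statistics section describe bleeding patients, and drains and suction more naturally yield low volumes than exact zeros. When 20% of patients were given 20 to 100 ml instead of zero (log-SD 0.8), the power loss vanished: 82% for the negative binomial and 77% for robust errors, with type I error 9.8% and 7.0%. At log-SD 0.6 type I error was 4.2% and 5.1%. This objection stands: the conservative scenario is conditional.

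**The test is not always wrong.** A reader might infer that only pure gamma data give about 5%. The 5.7% row above contradicts this, as does 4.8% at log-SD 0.8 with 5% zeros in a separate run. This stands too.

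**Unit dependence.** With zeros, the p-value changes if ml are rescaled (type I error 2.1% in ml and 9.7% in dl at log-SD 1.0 with 20% zeros). A reader might infer an open analytic choice, but the protocol fixes ml. The dependence is only a symptom of misfit.

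**Similar is not identical.** The wording may mean only the same covariates, and the detailed methodology is left to an analysis plan that is not shown. That plan may name a robust variance. But the text points to one model, "administered using negative binomial regression", and names no other for this outcome. The protocol also requires an amendment for substantial deviations. This objection limits the point without removing it.

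**Covariates lower the residual spread.** They do, but the inflation persists in the adjusted runs.

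**Conclusion.** The point holds in a limited form. By reference, the protocol assigns a count likelihood with model-based standard errors to a continuous volume. Those errors are valid only for near-gamma data without zeros.

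Under right-skewed log-normal volumes without zeros (log-SD 0.6 to 1.0, 60 per arm), type I error is about 8% to 16%, or 6% to 14% with one prognostic covariate. If about 20% of patients had exactly 0 ml, it would fall below about 3% at log-SD up to about 1.0, with roughly half the power of a robust analysis at log-SD 0.8. At log-SD 1.3 it would still be 8.8%. Intermediate mixtures can land near 5%.

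All of this rests on assumed distributions. Neither the direction nor the size of the error in this trial can be read from the protocol. The ratio of means in the two-arm model, the primary analysis and N = 120 are not affected.

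**What to change.** In Amount of blood loss, replace the reference to the primary endpoint's method with a named one: a log-link mean model (quasi-Poisson) for blood loss in ml, with sandwich standard errors and the same baseline covariates, reported as a ratio of means with its interval. This accepts zeros and does not depend on the unit.

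Add a small-sample correction to the sandwich variance, or a permutation or bootstrap p-value. Plain robust errors also run off nominal at this size, at about 4% to 9% (at most 9.5% in the runs here, at log-SD 1.3 with 30% zeros).

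Linear regression on log ml is not a good substitute. It is undefined at zero, and adding a constant brings back an arbitrary choice tied to the unit.

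The cost is one sentence in the protocol and the analysis plan, with no new data. The downsides are a somewhat wider interval than the negative binomial gives when volumes are skewed without zeros, and a slightly imperfect type I error if the correction is left out.

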##### Mortality

Time-to-event analysis (cox proportional hazard regression) evaluates the difference between the study groups, adjusted for age, disease scores (simplified acute physiology score (SAPS II), sequential organ failure assessment (SOFA score)) and reason for ICU admission.

##### Length of hospital stay

To evaluate the difference of length of hospital stay between the study group, a time-to-event analysis (cox proportional hazard regression) with hospital death as a competing risk will be performed adjusted for age, reason for ICU admission and disease scores (SAPS II, SOFA).

#### Interim analyses

A blinded analysis is planned after the recruitment of all 120 patients to assess the pre-defined effect size.

#### Safety analyses

Descriptive analysis and univariate tests will be performed for the number of SAE by severity grade, transfusion-related side effects, recurrent bleeding and the number of thromboembolic events within 48 h after study drug administration.

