## Study period overview

All patients needing platelet transfusion will be screened for study eligibility (Fig. 1). Upon enrolment, recruited patients will be randomised to one of the two treatment arms (i.e. platelet transfusion with vWF or placebo) with consecutive ICU follow-up for 2 days (Table 1). It will not be allowed to administer another dose of Wilate®/placebo for the study period of 48 h after the first dose was given.

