### Other outcome measures

Additional outcomes include the following:Platelet function analysis as assessed by VerifyNow ® ADP testAmount of administered coagulation factors: 4-factor prothrombin complex concentrate, calcium, tranexamic acid, fibrinogen concentrate, coagulation factor XIII concentrate, vitamin K, antithrombin concentrate and recombinant coagulation factor VIIaEstimate of costs for blood transfusion products during ICU stay (see Supplementary Table 1a and b)Thromboembolic complications

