### Safety outcome measures

#### Adverse events

An adverse event (AE) is any untoward medical incident in a patient or a clinical investigation participant administered a pharmaceutical product and which does not necessarily have a causal relationship with the study procedure. An AE can therefore be any unfavourable and unintended sign (including an abnormal laboratory finding), symptom or disease temporally associated with the use of a medicinal (investigational) product, whether or not related to the medicinal (investigational) product. [ICH E6 1.2] AEs are therefore difficult to detect in critically ill patients since the physical state leading to ICU admission itself may already lead to severe complications and further deterioration of physical and mental health.

ICU staff will be instructed to pay attention to allergic reactions like exanthema, flushing, urticaria, stridor, bronchospasm, shock and shortness of breath. These observations will be recorded together with the time of onset, duration, cessation, action that were taken, assessment of intensity and its relation to the study treatment. All adverse events will be reported to investigators and recorded by them on the participating patient’s data sheet during their following visits. Other extraordinary or questionable side effects will also be recorded. The occurrence of thromboembolic events will also be registered until the participating patients are discharged from the hospital.

Serious adverse events (SAEs) are classified as any medical occurrence that results in death, is life-threatening, requires prolongation of existing hospitalisation, or results in persistent or significant disability/incapacity. SAE reporting is required from the responsible Swiss authorities. The third criterion from the SAE definition will be excluded in our trial, as the occurrence of severe bleeding generally leads to prolongation of ICU and/or hospital stay.

A serious unexpected adverse drug reaction (SUSAR) indicates an adverse drug reaction that is of a nature or a severity inconsistent with the applicable product information. Transfusion-related side effects will therefore not be declared as SUSAR.

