^g^Including von Willebrand factor ristocetin cofactor (VWF:Rco); factors II, V, and VII; INR; and platelets count and level of thrombin

^h^Beriplex, Cyklokapron, Konakion, Kyberin, Fibrogammin, NovoSeven, ionised calcium, etc. (see Additional file 1: Table S1)

**Table 3 Tab3:** ICU follow-up data to be assessed within the 48-hour study period beginning at study drug administration

	***Metavision®***	RedCap®
Administration of study medication (or placebo)		
Platelet function analysis (VerifyNow® ADP test) 30–60 min after administration of study drug		X
Check if informed consent is possible		X
Amount of blood loss since drug administration		X
Cause of bleeding (if occurred)		X
SOFA score	X	
Vital parameters^a^	X	
Lowest temperature measured^b^		X
Acidosis occurred (pH < 7.35)		X
Duration of acidosis		X
Full blood count^c^	X	
Coagulation laboratory^d^	X	
ROTEM	X	
Level of vWF and FVIII	X	
Haemoglobin concentration	X	
Fluid balance^e^	X	
Number of given RBCs	X	
Number of given FFPs	X	
Number of given platelet concentrates	X	
Amount of Prothromblex after study intervention	X	
Amount of tranexam acid after study intervention	X	
Amount of fibrinogen after study intervention	X	
Name/amount of other given coagulation products^f^	X	
Number of revision surgery for haemorrhage control		X
Transfusion-related side effects (AE, SAE, see 3.7)^g^		X
Thromboembolic events		X
Any recurrent bleeding such as cerebral haemorrhage, DIC		X

^a^Blood pressure, pulse, SpO_2_, ScvO_2_, SvO_2_ and respiratory rate

^b^Lowest temperature measured since ICU admission

^c^Hemoglobin, leucocytes, erythrocites, haematocrit, mean corpuscular volume (MCV), mean corpuscular haemoglobin (MCH), mean corpuscular haemoglobin concentration (MCHC), red cell distribution width (RDW), thrombocytes, quick, international normalised ratio (INR), activated partial thromboplastin time (APTT), thrombin time 1 (TZ1), and fibrinogen^d^ including factors II, V and VII; INR; platelets count; and level of thrombin

^e^Since ICU admission until 48 h after the study drug administration

^f^Beriplex, Cyklokapron, Konakion, Kyberin, Fibrogammin, NovoSeven, ionised calcium, etc. (see above)

^g^48-h observation period

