## Thromboembolic complications

Any thromboembolic events (e.g. venous thromboembolism, pulmonary embolus, stroke, myocardial infaction) occurring during the study period will be recorded.

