## Safety

During the entire duration of the study, all adverse events (AE) and all serious adverse events (SAEs) are collected, fully investigated and documented in source documents and case report forms (CRF). Study duration encompassed the time from when the participant signs the informed consent until the last protocol-specific procedure has been completed, including a safety follow-up period.

Post-trial management will not differ from management during the study period and patients will be followed as described in the ‘Study period overview’ section.

An individual subject will be excluded from the study in case of the following:Withdrawal of consent by the independent physician or next of kinAn adverse event that in the opinion of the sponsor contraindicates further measuring (emergency setting)

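### Thromboembolic events are registered to hospital discharge but have a stated group comparison only to 48 h, and the SAE exclusion for prolonged stay is wider than its reason

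*Protocol article*

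**What the plan says.** **Capture of thromboembolic events.** The Adverse events section sets a long window: "The occurrence of thromboembolic events will also be registered until the participating patients are discharged from the hospital". Other places point to a shorter one:

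- Table 3 lists the events among "ICU follow-up data to be assessed within the 48-hour study period beginning at study drug administration".
- Table 1 marks adverse events at 30–60 min, day 1 and day 2, and not in the 30-day and 1-year column.
- The section Thromboembolic complications speaks of events "occurring during the study period will be recorded". Study period overview uses the same term in "for the study period of 48 h after the first dose was given".
- The Safety section, by contrast, states: "During the entire duration of the study, all adverse events (AE) and all serious adverse events (SAEs) are collected". It adds a safety follow-up period.

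**Analysis.** Other outcome measures lists "Thromboembolic complications" with no time window. Safety analyses plans descriptive analysis and univariate tests for SAEs by severity grade, transfusion-related side effects, "recurrent bleeding and the number of thromboembolic events within 48 h after study drug administration". The matching analysis section, Other outcomes of interest, covers only coagulation factors and costs.

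**SAE definition.** Four criteria are listed: death, threat to life, prolonged hospitalisation, and disability or incapacity. Then: "The third criterion from the SAE definition will be excluded in our trial, as the occurrence of severe bleeding generally leads to prolongation".

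**The concern.** The protocol singles out thromboembolic events for registration to discharge, so it treats later events as relevant. It then fixes a comparison that ends at 48 h. This is not detail left to the statistical analysis plan: a window is stated, and it is shorter than the protocol's own registration window.

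The SAE exclusion adds to the gap. A longer stay after severe bleeding explains why a stay prolonged by the bleeding says little about the drug. It does not explain why a stay prolonged by a thrombosis should be ignored.

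At stake is the safety conclusion on a product that, by the protocol's own account, supports platelet adhesion and aggregation and, through factor VIII, thrombin generation. The conflicting capture windows raise a practical risk too. Staff who follow Tables 1 and 3 could stop recording at 48 h, and the later events could then be lost.

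**Working it through.** The protocol gives no figure on this point to reproduce. The check is a comparison of the text, followed by an illustration of size.

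**Step 1: where does an event land?** Following the protocol as it stands:

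| Event | Thromboembolic comparison | SAE count |
|---|---|---|
| Within 48 h; fatal, life-threatening or disabling | yes | yes |
| Within 48 h; serious only through a longer stay | yes | no |
| After 48 h; fatal, life-threatening or disabling | no | yes, if the 48-h limit does not apply to SAEs |
| After 48 h; serious only through a longer stay | no | no |

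The condition in the third row arises because the sentence in Safety analyses does not make clear whether its closing 48-h phrase governs the whole list or only the last item. The fourth row does not depend on that reading: such an event enters neither comparison.

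**Step 2: what share falls within 48 h?** Not given. Assume a constant hazard over a stay of L days, so that the share is 2/L:

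- L = 4: 2/4 = 50%
- L = 7: 2/7 = 29%
- L = 14: 2/14 = 14%

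Both the constant hazard and the lengths of stay are assumptions. If risk is concentrated soon after dosing, the share is higher and could be most of the events.

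**Step 3: what does the window do to the information?** The input from the protocol is 60 patients per group. The in-hospital rates p1 and p2 and the share s within 48 h are assumptions. Expected events are 60 × s × (p1 + p2). Power is for a two-sided 5% test of two proportions by normal approximation, which is rough with so few events.

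| In-hospital rates | Window | Expected events | Power |
|---|---|---|---|
| 5% v 15% | to discharge | 60 × 0.20 = 12.0 | 45% |
| 5% v 15% | 48 h, s = 50% | 6.0 | 24% |
| 5% v 15% | 48 h, s = 20% | 2.4 | 12% |
| 10% v 20% | to discharge | 60 × 0.30 = 18.0 | 33% |
| 10% v 20% | 48 h, s = 50% | 9.0 | 18% |
| 10% v 20% | 48 h, s = 20% | 3.6 | 9% |

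**Step 4: precision to discharge.** For 5% v 15%, the standard error of the risk difference is √(0.05 × 0.95/60 + 0.15 × 0.85/60) = √0.00292 = 0.054. The 95% half-width is 1.96 × 0.054 = 0.106, so a 10-point difference would carry an interval of about −1 to 21 points. The longer window helps, but the comparison stays imprecise.

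**The case against.** The case on the other side has several parts.

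- **Safety analyses does not say that no other window will be used.** Thromboembolic complications are listed as an outcome without a limit, and details are deferred to a statistical analysis plan that is not shown. This is fair, and it is why the point is that later events have no stated comparison, not that they are thrown away.
- **Severe events are still seen.** Fatal, life-threatening and disabling events remain SAEs, and mortality and length of hospital stay are compared by group. This stands, subject to the unclear reach of the 48-h phrase for SAEs. Neither comparison identifies a non-fatal thrombosis as such.
- **An event that only prolongs the stay is still an adverse event to be collected.** True, but collection is not a comparison.
- **A 48-h window has merits.** The protocol equates 48 h with roughly four half-lives, and a fixed window is equally long in both groups, whereas time to discharge is not. That supports keeping 48 h, but not as the only window, since a clot formed during exposure may be diagnosed later.

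A reader might go further and infer that most of the drug's main harm goes uncompared. The documents do not support this. They give no event rate, time course or length of stay, and they do not call thrombosis the main expected harm; the first instruction to staff concerns allergic reactions. Nor does the one-sided 95% upper bound for 0 events in 60 patients, 1 − 0.05^(1/60) = 4.9%, show any loss from the short window, because it depends only on the number of patients. A reader might also infer that such events are kept out of the annual safety report. The protocol does not state that report's content.

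**Conclusion.** The point holds as a mismatch within the protocol. Registration runs to discharge, the only stated comparison runs to 48 h, and other sections and tables conflict on capture. The SAE exclusion covers every cause on a reason that covers bleeding only. The certain consequence is narrow: an event after 48 h whose only serious feature is a longer stay enters neither the thromboembolic comparison nor the SAE count.

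The number of events affected cannot be determined from the documents. The 14% to 50% range for the 48-h share rests wholly on a constant hazard and stays of 4 to 14 days. The change is worth making because it is cheap and bears on the safety conclusion; no large loss has been demonstrated.

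**What to change.** 1. In Safety analyses, compare by group the patients with at least one thromboembolic event from study drug to hospital discharge, giving counts and the risk difference with a confidence interval. Keep 48 h as an additional window. With 60 per group, the interval should carry more weight than the test.
2. In the same sentence, make clear whether the 48-h limit applies to the SAE count.
3. State one capture window for thromboembolic events and align Table 1, Table 3, Adverse events, Thromboembolic complications, Safety and Safety analyses with it.
4. Reconcile the exclusion of prolonged hospitalisation, which applies whatever the cause, with its stated reason, which concerns bleeding only.

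The cost is wording, one more table, a check that the case report form records events and their dates to discharge, and possibly a few more SAE reports. Precision will remain low.
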